## Abstract

**Background:**

The elimination of pathogenic microorganisms from the root canal system is one of the major steps required for successful endodontic treatment. The aim of the proposed study is to conduct a randomized, controlled, clinical trial for the clinical and radiographic evaluation of the effectiveness of photodynamic therapy during the endodontic treatment of primary teeth.

**Methods:**

Thirty primary anterior teeth in children aged 3 to 6 years old will be randomly divided into 2 groups: a control group, which will receive conventional treatment, and an experimental group, which will be subjected to photodynamic therapy. Microbiological evaluations will be performed before and after endodontic treatment. Moreover, clinical and radiographic evaluations will be performed on the day of treatment as well as 1, 3 and 6 months after treatment. Comparisons will be made of the two study groups. The data will be tabulated and presented in a descriptive, analytical fashion. Depending on the distribution (normal or non-normal), either the *t* test, ANOVA or the Mann-Whitney test will be used for analysis of the variables. The Wilcoxon test will be used for comparisons before and after treatment. *P* values < 0.05 (95 % significance level) will be considered indicative of statistically significant differences.

**Discussion:**

As successful endodontic treatment is directly related to intra-canal bacterial disinfection and consideringthe difficult task of endodontic treatment in primary teeth, often due to difficulties in controlling youngchildren, the internal anatomy of root canals and root resorption, the alternative of using PDT is a painless,easy-to-administer method that does not lead to microbial resistance and can assist in the achievement ofsuccessful endodontic treatment in primary teeth by eliminating the pain children can experience due to retreatmentas well as premature tooth loss.

**Trial registration:**

The protocol for this study was registered with Clinical Trials number NCT02485210 on 30 july 2015.

## Background

Dental caries and tooth injuries are the main causes of pulp inflammation in primary teeth. In cases of irreversible pulpitis or pulp necrosis, radical endodontic treatment is indicated, the aim of which is to avoid premature tooth loss and prevent harm to the tooth bud of the permanent successor [1–4].

Chronic periapical periodontitis is the major cause of the premature loss of primary teeth and it is widely accepted that this condition is related to endodontic infection [5]. The use of handheld files and irrigating solutions with disinfectant properties is currently the most common form of endodontic treatment. However, the existence of residual bacteria in many cases can lead to further infection of the root canal, which requires re-treatment or even extraction [3, 4, 6].

Pulp therapy in primary teeth is a complex matter due to difficulties in using dental instruments, the complexity of the apical delta, the biological cycle of primary teeth, physiological resorption and rhizolysis as well as a lack of cooperation on the part of the child and the need for long appointments [3, 6–10]. In primary teeth, this procedure should allow the resorption of root structures and the filling material within the normal period, which contributes to the eruption of the permanent successor without the occurrence of pathological resorption or radiolucency in the apical or furcation regions.

Any dental procedure that eliminated pain and the continuation of the pathological process was once accepted as satisfactory, but no longer. The minimum requirement of endodontic treatment is clinical and radiographic proof of treatment success and the remission of pathological processes [ 11, 12]. The elimination of pathogenic microorganisms from the root canal system is one of the essential steps to obtaining treatment success [3, 4, 7, 9, 10, 11, 13].

Photodynamic therapy (PDT) involves the use of a photosensitizer that is activated by light at a specific wavelength in the presence of oxygen. The transference of energy from the oxygen-activated photosensitizer results in the formation of a toxic oxygen species, known as singlet oxygen or free radicals. These are highly reactive chemical species that cause damage to proteins, lipids, nucleic acid and other microbial cell components [4, 7, 13–16]. It has been established that photosensitizers have a pronounced cationic charge and bond quickly to bacterial cells. Thus, photosensitizers exhibit a high degree of selectivity, killing microorganisms rather than host cells (available from: www.consort-statement.org).

PDT may be a viable option for achieving a reduction in pathogenic microorganisms during endodontic treatment, as this method is painless, easy to administer, does not lead to microbial resistance and has no systemic effects [4, 7, 15, 16]. PDT has been widely tested for the endodontic treatment of permanent teeth, demonstrating positive results in comparison to conventional treatment [13–16] (available from: www.consort-statement.org). However, few studies have evaluated the use of this type of therapy in primary teeth.

Considering the difficulties regarding the endodontic treatment of primary teeth and the knowledge that treatment success is directly related to bacterial decontamination of the root canal system, the effects of PDT for the endodontic treatment of primary teeth should be evaluated with the aim of improving this procedure.

The aim of the proposed study is to conduct a randomized, controlled, clinical trial for the clinical and radiographic evaluation of the effectiveness of PDT during the endodontic treatment of primary teeth.

## Methods

### Ethical considerations

The proposed study will be conducted in compliance with the regulatory norms governing research involving human subjects and has received approval from the institutional review board of University of Nove de Julho (São Paulo, Brazil) under process number 832.657. Following clarifications regarding the objectives and procedures, the parents/guardians of the participants will sign a statement of informed consent authorizing the participation of their children in the study, as stipulated in Resolution 196/96 of the Brazilian National Board of Health.

### Subjects

Thirty primary anterior teeth will be selected in health male and female children with no ethnicity restriction. The teeth must be with diagnosis of dental caries or trauma with pulp envolvement. The children will be recruited at pediatric dentistry of University os Nove de Julho (São Paulo - Brasil). The parents or legal guardian will sign the statement of informed consent. Based on a previous study by Pinheiro et al. [7] for sample size calculation it was considered the standard desviation (2.41) and the diference to be detected in the median of colony forming units per milimiter (CFU/ml) before and after PDT 2.9, with significance level of 5 % and power of 95 %.

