### Data organization and statistical analysis

The data will be tabulated and presented in a descriptive and analytical manner. Descriptive statistics will involve the determination of frequency, mean and standard deviation values. The Kolmogorov-Smirnov test will be used to determine the distribution of the data (normal or non-normal). Depending on the distribution, differences between groups regarding mean CFU and percentage reduction in bacteria will be determined using either the *t* test, analysis of variance (ANOVA) or the Mann-Whitney test. The Wilcoxon test will be used for comparisons before and after treatment. *P* values < 0.05 (95 % significance level) will be considered indicative of statistically significant differences. All statistical analyses will be conducted with the aid of the SPSS 21 program (SPSS Inc., Chicago, IL, USA).

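### The sample size rests on a before-after change under PDT, so the stated 95% power does not carry over to the planned comparison of two arms of 15 teeth

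*Protocol article*

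**What the plan says.** The sizing is in the protocol article, Methods, Subjects. The plan is that "Thirty primary anterior teeth will be selected". An earlier study supplied both inputs. On the spread, the text says "it was considered the standard desviation (2.41"). The effect is a difference "to be detected in the median of colony forming units per milimiter (CFU/ml) before and after PDT 2.9". The error rates come last, in the words "with significance level of 5 % and power of 95" per cent. The paragraph does not name the test, the sidedness, the scale (raw or log10 CFU/ml), or whether 2.41 is the SD of one measurement or of a change.

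Table 1, under Randomization, splits the teeth into 15 for conventional treatment and 15 for conventional treatment plus PDT.

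The section on data organization and statistical analysis keeps two comparisons apart. For the arms it reads "differences between groups regarding mean CFU and percentage reduction in bacteria will be determined using either the" and then names three options: a t test, ANOVA and Mann-Whitney, judged at P < 0.05. Within teeth, the rule is separate: "The Wilcoxon test will be used for comparisons before and after treatment".

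**The concern.** The effect that sizes the trial and the effect that randomisation is there to estimate are different quantities. A before-after change under PDT says how far counts fall in treated teeth. The arms differ only by whatever PDT adds to a control that is itself active. According to the two Interventions lists, both arms are filed and irrigated with 1% sodium hypochlorite between the first and second bacterial samples.

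Two things follow. First, the 95% cannot be read as the power of the between-arm test unless 2.9 also happens to be the between-arm difference and the test is one-sided. Second, if 2.9 spans the preparation step and control counts fall as well, the between-arm difference is below 2.9 and power falls with it. What is at stake is how a non-significant result between arms is read: set against a claimed 95% power, it would look like stronger evidence of no benefit than the design can give.

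**Working it through.** **Inputs.** Difference 2.9, SD 2.41, level 5%, power 95% (Subjects); 15 teeth per arm (Table 1). Standardised difference: d = 2.9 / 2.41 = 1.203.

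**Step 1. Reproduce the 15 per arm.** The two-sample normal approximation is n per arm = 2 (z_alpha + z_power)² / d².

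- One-sided 5%: 2 × (1.645 + 1.645)² / 1.203² = 14.95, so 15. This matches Table 1.
- Two-sided 5%: 2 × (1.960 + 1.645)² / 1.203² = 17.95, so 18.

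The stated size can therefore be recovered as a one-sided two-sample calculation that uses 2.9 as if it were a between-arm difference. With the t distribution, even the one-sided version gives 94.2% power at 15 and needs 15.68, so 16 per arm.

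**Step 2. Power of the between-arm test as planned, taken as two-sided, if the between-arm difference were 2.9.**

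| Method, 15 per arm, two-sided 5% | Power at 2.9 | Teeth per arm for 95% |
|---|---|---|
| Normal approximation | Φ(1.203 × √7.5 − 1.960) = Φ(1.335) = 90.9% | 17.95, so 18 |
| t test (noncentral t) | 88.9% | 18.97, so 19 |
| Mann-Whitney | 86-87% (simulated, normal data) | about 20 (18.97 / 0.955 = 19.86) |

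The difference detectable with 95% power by the two-sided t test at 15 per arm is 3.29.

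**Step 3. The before-after reading.** For a paired t test, two-sided 5%, 95% power, the answer depends on what 2.41 is. If it is the SD of one measurement and r is the before-after correlation (an assumption; the article gives none), the SD of the change is 2.41 × √(2(1 − r)).

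| Reading of 2.41 | SD of change | Teeth for 95% | Power with 15 teeth |
|---|---|---|---|
| SD of the change | 2.41 | 11.1, so 12 | 99.1% |
| SD of one measurement, r = 0 | 3.41 | 19.98, so 20 | 86.5% |
| SD of one measurement, r = 0.28 | 2.89 | 14.99, so 15 | 95.0% |

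A two-sided paired calculation can thus also land on 15, for a suitable correlation. The article does not say which route was used. On the paired route, the 95% would describe the PDT arm's own change and not the contrast between arms.

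**Step 4. Smaller between-arm differences.** The article gives no between-arm difference, so the values below are assumptions. Two-sided t test, 15 per arm, SD 2.41:

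| Assumed between-arm difference | d | Power |
|---|---|---|
| 2.9 | 1.203 | 89% |
| 2.0 | 0.830 | 59% |
| 1.45 | 0.602 | 36% |
| 1.0 | 0.415 | 20% |

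**The case against.** A reader might infer that the sample size contains an arithmetic slip, and that the true power is 89% where the article says 95%. The article does not support that. It never says that the 95% belongs to a two-sided between-arm test, and its inputs give 15 per arm exactly by the one-sided formula. Nor can one say that 15 arises only that way, since a two-sided paired calculation also gives 15 at a correlation of about 0.28. For the before-after change that the Subjects section names, 15 teeth give 99.1% power if 2.41 is the SD of the change, so on that reading 95% is exceeded.

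The 89% is itself conditional. It takes 2.9 as a between-arm difference, which is not how the article describes it. If the earlier study measured *before* after canal preparation, 2.9 would be the increment from PDT and a fair proxy for the difference between arms. If it measured before preparation, 2.9 may be too large. The article does not settle this, so the figures at 2.0, 1.45 and 1.0 illustrate sensitivity and do not predict the trial's power.

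Bacterial counts are also not the only randomised comparison. Clinical and radiographic success is assessed in both arms and is the stated aim. The sample-size paragraph concerns CFU alone, and this point is limited to that.

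What stands against the objection is that none of these routes makes 95% the power of the planned between-arm test. The paired route concerns another contrast. The one-sided route needs a direction that the article never states, and the analysis section speaks of differences without direction and lists ANOVA, which has none. Reading the tests as two-sided is an inference, but the natural one. Nor is this a detail left to an analysis plan, because the inputs, the level, the power and the arm sizes are all stated in the article.

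**Conclusion.** Wrong as written: the sizing does not match the planned comparison. The stated 95% comes from a before-after change, and the article gives no between-arm difference from which the power of the randomised CFU comparison could be calculated.

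The size of the gap is conditional. If the between-arm difference is 2.9, the SD is 2.41 on the scale analysed, and the test is two-sided at 5%, then power is about 6 percentage points below the stated figure for a t test (95 − 88.9 = 6.1) and 8 to 9 points below for Mann-Whitney. That is still a well-powered comparison. The larger risk is that the true difference is smaller because control counts also fall; the article leaves that open. An arithmetic error is not shown.

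**What to change.** Keep 30 teeth and rewrite the sample-size paragraph for the between-arm comparison. It should:

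- name the outcome scale (raw or log10 CFU/ml) and say whether 2.41 is the SD of one measurement or of a change;
- state a two-sided 5% level;
- say that 2.9 was a before-after change under PDT in the earlier study and is not an established between-arm effect;
- replace the 95% with a conditional statement, for example: *With 15 teeth per arm, power is about 89% (t test) or 86-87% (Mann-Whitney) if the between-arm difference is 2.9 and the SD 2.41; 95% power holds only for a difference of about 3.3 or more*;
- add the power at smaller assumed differences, for example 59% at 2.0, because the control treatment is active.

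The cost is one paragraph and a less favourable stated power. No teeth are added and no test changes. If 95% two-sided power at 2.9 is to be kept instead, the price is 19 teeth per arm for the t test, 38 in all, or about 40 in all for Mann-Whitney.

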### Inclusion criteria

Children aged 3 to 6 years, with at least 1 primary anterior tooth with irreversible pulpitis or pulp necrosis due to caries or trauma suitable for restoration, and at least two thirds of the root remaining; otherwise health patients who have not been submitted to antibiotic therapy in the previous 3 months.

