### Exclusion criteria

Compromised health, primary teeth with more than one third root loss, lack of internal pathological resorption, impossibility of restoration, cases of re-treatment and crypt involvement.

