### Experimental groups

#### Randomization

The type of treatment will be randomly determined for each tooth using tiles on which 1 of 2 numbers is printed (Table 1):

**Table 1 Tab1:** Experimental groups

Experimental groups	
Group I (*n* = 15)	Conventional endodontic treatment
Group II (*n* = 15)	Endodontic treatment with administration of PDT

*PDT* photodynamic therapy

Number 1: conventional treatment (Group I).Number 2: treatment with PDT (Group II).

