### Clinical and radiographic evaluations of teeth

The clinical evaluations will be performed with the child in a dental chair under the light of the reflector, with the aid of a mouth mirror and palpation of the area around the affected tooth. During the initial exam as well as the follow-up exams at 1, 3 and 6 months after endodontic treatment, the following clinical data will be recorded: history of spontaneous pain indicative of apical periodontitis, presence of fistula or abscess, gingival swelling and pathological tooth mobility. The radiographic exams will involve the evaluation of signs of radiolucency in the periapical region and pathological root reabsorption.

The data collected during the initial exam as well as the follow-up exams at 1, 3 and 6 months after endodontic treatment and the comparison of the initial diagnostic radiographic exam to the radiographic exams at 1, 3 and 6 months after treatment will constitute the basis for the evaluation of the treatment success or failure. The radiographs will be analyzed by two experienced examiners with the aid of a negative viewing box (negatoscope). These examiners will not receive any information regarding the type of treatment each tooth received. Cases of divergence will be resolved by consensus between the two examiners [17].

The following criteria will be used for the determination of treatment success or failure:Complete repair (= success)Clinically: absence of signs and symptoms;

Radiographically: absence of pathological root resorption, normal width of periodontal ligament space, absence of lesion development in periapical regions in cases of absence of lesion in the initial diagnostic radiograph and complete regression of lesion in cases of presence of lesion in the initial diagnostic radiograph.2.Incomplete repair (= success)Clinically: absence of signs and symptoms;

Radiographically: absence of pathological root resorption and reduction lesion size in the periapical region.3.Lack of repair (= failure)Clinically: signs and symptoms indicative of acute apical periodontitis;

Radiographically: presence of pathological root resorption, lesion in furcation/periapical region unchanged in size during follow-up period, increase in lesion size or the development of a new lesion [17].

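### Pulpitis and necrotic teeth are pooled in an unstratified draw with no requirement of a positive first culture, so percentage reduction is undefined for some eligible teeth and the CFU comparison may be diluted

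*Protocol article*

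**What the plan says.** All references are to the protocol article.

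- **Inclusion criteria.** Two pulp diagnoses qualify on the same footing: "with at least 1 primary anterior tooth with irreversible pulpitis or pulp necrosis due to caries or trauma suitable for restoration".
- **Exclusion criteria.** The list is "Compromised health, primary teeth with more than one third root loss, lack of internal pathological resorption, impossibility of restoration, cases of re-treatment and crypt involvement". It sets no condition on pulp vitality, bacteria in the first sample or presence of a lesion.
- **Randomization.** "The type of treatment will be randomly determined for each tooth using tiles on which 1 of 2 numbers is printed". Table 1 gives 15 teeth per group. No stratum is named.
- **Interventions.** In both groups the first bacterial sample is taken before canal preparation, and so before any PDT.
- **Data organization and statistical analysis.** "differences between groups regarding mean CFU and percentage reduction in bacteria will be determined" by t test, ANOVA or Mann-Whitney. Neither diagnosis nor the first count is mentioned.
- **Clinical and radiographic evaluations of teeth.** The lesion criterion for complete repair depends on the starting point. A tooth that starts without a lesion needs "absence of lesion development in periapical regions in cases of absence of lesion in the initial diagnostic radiograph"; a tooth that starts with one needs regression. A new lesion counts as failure.
- **Subjects.** One SD and one difference serve for all teeth: "it was considered the standard desviation (2.41" and "before and after PDT 2.9, with significance level of 5 % and power of 95" per cent.

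**The concern.** The Background justifies PDT by one mechanism, the killing of microorganisms in the canal. The two diagnoses may differ in how much there is to kill. If some eligible teeth start with few or no culturable bacteria, the plan has two difficulties.

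First, one of its two named microbiological measures has no value for a tooth with a negative first culture, and the other can only stay level or worsen. The plan has no rule for these teeth. Leaving them in pulls both groups towards the same result; dropping them after the data are seen invites selective handling.

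Second, diagnosis may affect outcome, and with 15 teeth per group an unstratified draw can leave it visibly uneven. The result would then be hard to interpret in either direction.

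**Working it through.** **1. The plan's own sample size.** Inputs from Subjects: SD 2.41, difference 2.9, alpha 5%, power 95%. Normal formula for two groups: n = 2 × [SD × (z_alpha + z_power) / difference]².

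- One-sided: 2 × [2.41 × (1.645 + 1.645) / 2.9]² = 14.95, so 15 per group. This reproduces Table 1.
- Two-sided: 2 × [2.41 × (1.960 + 1.645) / 2.9]² = 17.95, so 18 per group.

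The text describes 2.9 as a before/after difference. Using it as a between-group effect, as below, is an assumption.

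**2. A tooth with a negative first culture.** Percentage reduction = 100 × (first − second) / first. With first = 0 this is undefined. The change, first − second, is at most 0.

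**3. Dilution, as illustration only.** Let f be the share of teeth that cannot respond. The documents do not give f; 20% to 50% is assumed. The mean difference becomes 2.9 × (1 − f). Power is for a two-sided t test with 15 per group, 28 degrees of freedom and noncentrality = difference / (2.41 × √(2/15)).

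| f | Mean difference | Power |
|---|---|---|
| 0 | 2.90 | 89% |
| 20% | 2.32 | 72% |
| one third | 1.93 | 56% |
| 50% | 1.45 | 36% |

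This holds the SD at 2.41. Simulation under other scatter assumptions gives, for f = 20%, one third and 50%:

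- Non-responders fixed at zero change, control teeth with no mean reduction: 77%, 66%, 49%.
- Non-responders with full scatter: about 67%, 50%, 31%.
- Non-responders fixed at zero, responsive control teeth falling by an assumed 3 units: 57%, 40%, 25%.

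The direction is the same throughout; the size is not fixed by the documents.

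**4. Restricting to responsive teeth.** Effect 2.9, SD 2.41, two-sided t test: 12 per group (f = 20%) gives 80%, 10 per group (one third) gives 72%, and 8 per group (about 50%) gives 61%. Each exceeds the diluted figure for the same f, despite fewer teeth.

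**5. Chance imbalance.** With K pulpitis teeth among 30 split exactly 15/15, the number in one group is hypergeometric. For K = 10, a gap of 4 or more means at most 3 or at least 7 in one group: 2 × (0.0001 + 0.0025 + 0.0225 + 0.0975) = 0.245. For K = 15, a gap of 5 or more has probability 0.143. K is also an assumption.

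**6. Whether separate tile sets cure this.** Two large sets, each with 15 ones and 15 twos, do not: 10 pulpitis teeth drawn from such a set face the same hypergeometric split, so the chance of a gap of 4 or more is again 24.5%. A set of two ones and two twos, refilled when empty, caps the gap at 2 within each diagnosis, because only the last unfinished block can be uneven.

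**The case against.** - **The population is the one that receives the procedure.** The Background gives irreversible pulpitis and pulp necrosis together as the indications, and the stated aim is clinical and radiographic. This stands: enrolling both is legitimate. It does not supply a value for an undefined percentage reduction.
- **Nothing says that pulpitis canals are sterile.** This also stands. The documents give neither the share of pulpitis teeth nor their bacterial load. Pulpitis and culture-negative are also different groups: the power figures depend on the second, the imbalance figures on the first. All of them are conditional.
- **Lesion-free teeth.** A reader might infer that a tooth without an initial lesion cannot show a PDT effect on repair. The repair criteria do not support that. Such a tooth still fails on a new lesion, pathological resorption or signs and symptoms, and PDT could prevent any of these. It faces a different success standard, not an impossible one.
- **Imbalance as bias.** A reader might also infer that the pooled draw biases the trial. It does not: randomization is unbiased on average, and the test's error rate already covers chance imbalance. What remains is lost precision and a result that is harder to defend.
- **Analysis rules may sit in a fuller document.** This is fair for covariates and subgroup tables. Eligibility, allocation and the named CFU measures, however, are fixed in this text, and stratification cannot be applied to teeth already drawn.

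**Conclusion.** The point holds in limited form and should be acted on. From the text alone: two diagnoses are pooled, the draw has no strata, no positive first culture is required, and percentage reduction is undefined for any tooth whose first culture is negative. Such teeth dilute the CFU comparison by an amount that the documents do not give.

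The fall in two-sided power from 89% to roughly 72–36% rests on three assumptions: 2.9 and 2.41 apply between groups, 20–50% of teeth cannot respond, and scatter is unchanged. The other scatter models tried move the 20% figure between 57% and 77%, and the 50% figure between about 25% and 49%. The roughly 25% chance of a gap of four or more pulpitis teeth assumes 10 such teeth in 30.

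**What to change.** 1. **Allocation.** For teeth still to be enrolled, draw tiles separately for irreversible pulpitis and for necrosis, in small blocks (for example two 1s and two 2s, refilled when empty). Include diagnosis as a factor in the between-group comparison. The ANOVA already listed allows this; if the rank test is used, take a stratified version.
2. **CFU analysis set.** State that mean CFU and percentage reduction are compared in teeth whose pre-treatment sample grows bacteria. Keep all teeth in the clinical and radiographic follow-up. That sample precedes canal preparation and PDT in both groups, so the restriction does not bias the comparison.
3. **Optional.** Show repair by initial lesion status in a descriptive table.

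**Cost.** A second set of tiles and a few lines of text; no extra sample or visit. The overall split may differ slightly from 15/15. The CFU comparison will contain fewer teeth, and its conclusion will be limited to culture-positive canals. The Trial status section says that recruitment began in September 2015 and was planned to run to December 2015, so item 1 can help only teeth not yet drawn. Items 2 and 3 can still be fixed before the results are examined.
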